#### Measures

Table 1 summarizes the measures used for Objective 2, including their corresponding survey time points across the study. Measures span demographics, mental health, smoking, HIV-related variables, and intervention acceptability, with administration occurring from prescreener through postinterview assessments.

**Table 1. T1:** Objective 2 measures.

	Items	Prescreener survey	Preinterview survey	Interview survey	Postinterview survey
Demographics and background					
Demographic questionnaire^a^	24	✓	✓		
Mental health variables					
Short Scale Anxiety Sensitivity Index^a^ [59]	5	✓			
Smoking variables					
Smoking History Questionnaire^b^ [61]	18		✓		
Motivation to quit^a^	1	✓			
Heaviness of Smoking Index^b^	2	✓			
HIV-related variables					
HIV status and history^b^ (self-report or chart review)	1	✓			
AIDS Clinical Trials Group adherence questionnaire^b^ [62]	10		✓		
Index of engagement in HIV care^b^ [63]	10		✓		
Intervention acceptability variables					
Perception of intervention content^c^ [60]	6			✓	
Qualitative interview	24			✓	
Credibility/expectancy questionnaire^d^ [64]	6				✓
Advertisement attitudes measure^d^ [65]	5				✓
Iowa Cultural Understanding Assessment-Client Form^d^ [66]	15				✓

a Eligibility or screening.

b Preinterview descriptors.

c Per-video ratings.

d Postinterview global measures.

##### Demographics and Screener Questions

Participants were asked to provide standard demographic information (ie, name, contact information, age, sex, race, ethnicity, brief smoking history, etc). Participants also provided their language preference. Select items were used as eligibility criteria. Name and contact information were used for scheduling and interview purposes and will not be part of the dataset.

##### Anxiety Sensitivity

AS was assessed using the SSASI [59]. The SSASI is a 5-item measure that was used to provide a descriptive assessment of AS at prescreener by using a 5-point Likert scale (0=very little to 4=very much). The SSASI was used as the AS eligibility criteria at prescreener.

##### Smoking Behavior

Smoking behavior was collected during the preinterview. The Smoking History Questionnaire [61] is an 18-item self-report questionnaire used to assess smoking history, pattern, and use of evidence-based pharmacological and nonpharmacological cessation treatment (“Since you started regular smoking, what is the average number of days per week you smoke?”). This measure was used to evaluate an individual’s current smoking habits.

##### Motivation to Quit

Motivation to quit smoking, an eligibility criterion, was assessed at the prescreener using the following question: “On a scale from 0 to 10 with 0 being ‘not at all motivated’ and 10 being ‘extremely motivated’, how motivated are you to quit smoking in the next month?”

##### Nicotine Dependence

The Heaviness of Smoking Index [67] measures nicotine dependence and the intensity of nicotine addiction. Participants answered 2 questions based on their smoking habits (“On days that you smoke, how soon after you wake up do you smoke your first cigarette?” and “How many cigarettes do you typically smoke per day?”). This measure was collected at preinterview for descriptive purposes.

##### HIV Status and History

Participants answered whether they had ever been diagnosed with HIV and when they were first diagnosed with HIV at the prescreener to determine eligibility. HIV status was reported via chart review if the participant was a clinic patient or via self-report. If self-reporting, participants presented their ART medication with their name and the medication name visible, documentation of their diagnosis, or their most recent viral load assessment.

##### HIV Treatment–Related Variables

The AIDS Clinical Trials Group Adherence Questionnaire [62] assesses ART adherence and reasons for missed medication and nonadherence across 20 items (“How sure are you that your HIV management medication will have a positive effect on your health”). HIV treatment engagement was assessed using the Index of Engagement in HIV Care [63], a 10-item scale that asked participants about their experience of HIV care (“How much do you trust your HIV care provider?”). HIV treatment–related measures were collected at preinterview and will be used for descriptive purposes.

##### Qualitative Interview

The semistructured qualitative interview assessed ways to improve the animated videos and scripted content (Multimedia Appendix 1). The question path was developed based on previous formative interview question paths [40], then modified to assess video content for cultural relevance, ease of understanding, and to solicit input for additional content to increase clarity and acceptability. The question path was tested prior to implementation. Participants first completed a set of quantitative questions from the Perception of Intervention measure, which was adapted from prior work [60]. The Perception of Intervention Content measure was administered immediately after each video and prior to the video-specific qualitative interview questions. The Perception of Intervention Content measure assessed quantitative ratings of personal relevance, clarity of understanding, perceived helpfulness for understanding smoking-stress and smoking-HIV links, and motivation to improve HIV care and reduce smoking. These immediate postvideo ratings capture participants‘ initial reactions and will be used to identify video segments that may require targeted refinement. Qualitative interview questions (e.g., “What could we change about this video to make it more interesting or more motivating for you?”) were asked following the Perception of Intervention Content measure, and statements to which participants responded “Strongly Disagree,” “Neither Agree nor Disagree,” or “Disagree” were probed during the qualitative interview. For example, “I see that you responded neutral or disagreed with the statement ‘(repeat the statement they disagreed with)’. Tell me about your ‘neutral‘ or ‘disagree’ response here. I’d like to understand that.” Finally, participants were asked a set of qualitative questions to gather their impressions of all 4 videos as a group (eg, “Can you think of an example where one of the videos talked about smoking or HIV in a way that fit with [Mexican/Mexican American, Central American, South American] culture?”).

##### Intervention Acceptability Variables

The interview and postinterview survey were used to assess intervention acceptability. The Credibility/Expectancy Questionnaire [64] is a 6-item measure regarding perceptions of treatment credibility and expectancies about treatment, along with acceptability and satisfaction (“At this point, how successful do you think the app content would be in helping you quit smoking?”). Moreover, the Advertisement Attitudes Measure [65] is a 5-item subscale that assessed intervention relevance (“The videos were meaningful.”). Finally, the Iowa Cultural Understanding Assessment-Client Form [66], a 15-item measure evaluating the intervention’s cultural competence, was provided at postinterview.

### Data Analysis

#### Quantitative Data

Quantitative analyses will focus on descriptive statistics (means, SDs, and response distributions) for intervention acceptability measures collected at 2 levels. Video-specific acceptability will be assessed using the Perception of Intervention Content measure, administered immediately after each video and prior to the video-specific qualitative interview questions. The Perception of Intervention Content measure ratings will be summarized at the item and video levels to identify patterns in perceived relevance, comprehension, and motivational impact across intervention components and to identify specific video segments that may require refinement. Global postinterview acceptability will be assessed using the Credibility/Expectancy Questionnaire, Advertisement Attitudes Measure, and Iowa Cultural Understanding Assessment-Client Form. These measures capture overall perceptions of intervention credibility, satisfaction, perceived effectiveness, relevance, and cultural competence across the intervention as a whole. Quantitative acceptability findings will distinguish between video-specific refinement needs (informed primarily by the Perception of Intervention Content measure ratings) and broader intervention-level acceptability considerations (informed by global postinterview measures). Quantitative acceptability ratings will be used to identify specific and overall intervention components demonstrating lower perceived clarity, relevance, usefulness, credibility, or cultural appropriateness that may warrant refinement.

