**Figure 1. F1:**
[figure not shown]
Participant flowchart. HIPAA: Health Insurance Portability and Accountability Act.

During the interview, participants reviewed 4 (out of 20) culturally tailored videos (3‐5 min each) in the language of their preference (Spanish or English) that were linguistically specific to their subgroup. The 20 videos for each language and subgroup were divided into 5 groups of 4 videos based on the overall topic of the video (Stress, Nicotine Replacement Therapy, Flexible Thinking, Mindfulness, and Managing Uncomfortable Sensations). Qualtrics randomly assigned which group of videos each participant viewed during the interview. A quota system was used so that each group of 4 videos was removed from the rotation after being viewed 7 times. Although some videos may reference content in other videos, the materials were appropriate to be reviewed on their own. Following each video, participants completed a brief survey on content relevance, appropriateness, ease of understanding and clarity, usefulness, and helpfulness [60]. After completing the survey, research staff followed a semistructured interview guide to assess video impressions, identify opportunities to improve content tailoring, gather suggestions for additional topics to include, and assess the relevance of the content. Semistructured interview guides also explored how sociocultural factors may be appropriately integrated into the content (eg, potential interpersonal, stigma, social, family, and religious considerations). The interview portion for all participants was recorded, and after the interview was completed, the audio file was transcribed and translated using a professional transcription and translation service. Following transcriptions, each video recording was deleted.

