**Figure 2. F2:**
[figure not shown]
Mixed methods integration framework.

Lower Perception of Intervention Content ratings will be examined alongside participants’ explanations to identify specific content elements contributing to reduced clarity, relevance, or motivational impact. Global acceptability measures will contextualize overall perceptions of intervention credibility, usefulness, and cultural appropriateness across intervention materials. For example, videos receiving lower quantitative ratings (eg, clarity or cultural relevance) will be reviewed alongside corresponding qualitative feedback to determine specific revision targets.

Integrated findings will be synthesized into actionable revision targets, with priority given to content areas showing convergence between lower quantitative ratings and recurrent qualitative suggestions. Content demonstrating consistently favorable ratings and minimal suggested changes will be retained. Integrated results will directly inform iterative refinement of intervention materials and determination of readiness for subsequent feasibility and implementation testing.

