### Sample Size Determination

A total of 80 participants were enrolled to ensure a sufficient sample for identifying patterns across diverse Hispanic subgroups and to reach thematic saturation in qualitative analysis [71]. Recruitment across Mexican/Mexican American, Central American, and South American participants was intended to be approximate and guided by local clinic demographics and recruitment feasibility rather than fixed subgroup targets (a maximum of 35 and a minimum of 10 per subgroup). Recruitment was monitored throughout the study to support representation across subgroups, and outreach could be prioritized for underrepresented groups as needed to obtain sufficient feedback to inform linguistic tailoring. This distribution reflected the relative prevalence of these subgroups in the study’s recruitment areas and enabled meaningful, culturally specific feedback while maintaining feasibility for a pilot study. Representation across subgroups strengthened the cultural validity of the intervention materials and supported tailored refinement decisions based on thematic saturation and relevance of feedback rather than equal subgroup sample sizes.

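### The three global post-interview measures are described as covering the whole intervention, but each participant rated it after seeing one randomly assigned topic set of 4 of the 20 videos

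*Protocol article*

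**What the plan says.** Under Procedures (Objective 2), "participants reviewed 4 (out of 20) culturally tailored videos". The 20 videos for each language and subgroup were "divided into 5 groups of 4 videos based on the overall topic of the video", and "Qualtrics randomly assigned which group of videos each participant viewed during the interview". Under the quota, "each group of 4 videos was removed from the rotation after being viewed 7 times".

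Table 1 and Intervention Acceptability Variables place the Credibility/Expectancy Questionnaire, the Advertisement Attitudes Measure and the Iowa form at the post-interview survey only, so each is completed once, after the assigned set.

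The Quantitative Data section then says: "These measures capture overall perceptions of intervention credibility, satisfaction, perceived effectiveness, relevance, and cultural competence across the intervention as a whole". It uses these measures for intervention-level acceptability and reserves summaries by item and video for the Perception of Intervention Content measure. The mixed-methods section repeats the reading: "Global acceptability measures will contextualize overall perceptions of intervention credibility, usefulness, and cultural appropriateness across intervention materials". The Limitations section does not mention that each person saw one fifth of the content.

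**The concern.** The sets were formed by topic: stress, nicotine replacement, flexible thinking, mindfulness, and uncomfortable sensations. Four videos from one set are therefore not a cross-section of the programme. A participant shown only the mindfulness set and one shown only the nicotine replacement set answer the same credibility and cultural-fit items about different material. Each score belongs to one set, and describing it as a perception of the whole claims something the design does not provide.

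Two things are at stake. First, a reader may take the global scores as coming from people who reviewed the full programme. Second, the plan wants its ratings to locate components that are weak on credibility or cultural appropriateness, among other dimensions. A single figure averaged over sets is a poor tool for that, because a deficit in one set is mixed with four sets that do not share it.

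**Working it through.** **Inputs.** From Procedures: 20 videos, 4 seen per participant, and a quota of 7 views per set. From Sample Size Determination: "A total of 80 participants were enrolled", with subgroup limits of "a maximum of 35 and a minimum of 10 per subgroup". The realised subgroup and set sizes are not given, nor is any SD for the global measures.

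**The plan's own figure.** 20/4 = 5 sets, and 5 × 7 = 35, which equals the stated subgroup maximum. This suggests that the quota ran within each subgroup, since 35 places in all could not hold 80 people. I assume that below. The total of 80 has no formula behind it to reproduce.

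**Exposure.** 4/20 = 20% of the videos per participant. Expected participants per set: 80/5 = 16.

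**What a pooled mean shows.** If one set lies d below the other four and a share w of participants saw it, the pooled mean falls by w × d.
- Expected share: w = 16/80 = 0.20, so a deficit of d appears as 0.20d, a fivefold dilution.
- Illustration with an assumed d = 1 SD: the pooled mean falls by 0.20 SD.
- Illustration on an assumed 1–9 scale: four sets at 7 and one at 4 pool to (4 × 7 + 4)/5 = 6.4.

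**How far w can move.** The quota is only a cap. I simulated random assignment with a cap of 7 per set within subgroup, 4,000 runs for each assumed split of the 80:

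| Assumed subgroup sizes | Central 95% range of w |
|---|---|
| 35/35/10 | 0.175 to 0.2375 |
| 35/30/15 | 0.15 to 0.25 |
| 35/25/20 | 0.1375 to 0.25 |
| 27/27/26 | 0.125 to 0.2625 |

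The upper limit under this quota is 3 × 7 = 21 of 80, or 0.2625. Dilution therefore runs from 1/0.2625 = 3.8-fold to 1/0.125 = 8-fold.

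**What a by-set summary shows.** The full d appears. For n = 16 the 95% half-width is t(15)/√16 = 2.131/4 = 0.53 SD. Over the range of w, set sizes run from 0.125 × 80 = 10 to 21, giving half-widths from 2.262/√10 = 0.72 SD down to 2.086/√21 = 0.46 SD. One set against the rest has standard error √(1/16 + 1/64) = 0.28 SD, so a 1 SD deficit is about 3.6 standard errors and a 0.5 SD deficit about 1.8. A large deficit would stand out by set; a moderate one might not.

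**Limit on finer breakdown.** In a subgroup of 10, a set is seen by 10/5 = 2 people on average and by nobody in about 10% of simulated runs. A set-by-subgroup table could carry counts but little else.

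**The case against.** The strongest reply is that this is a matter of wording, and much of that reply stands.

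- **Pooling is not stated.** A reader might infer that the plan commits to one pooled score and rules out a by-set summary. It does not say so. A condensed article can leave such a table to a fuller plan, and the aim of finding specific components low on credibility even hints at a component-level look.
- **The pooled mean is not invalid.** Sets were assigned at random, so it estimates average acceptability over the five sets, which is a sensible summary. Only its description is wrong.
- **A weak set would not necessarily go unseen.** Ratings follow every video, neutral and negative answers are probed at once, and the interview closes with questions on all four videos together, including cultural fit.
- **No decision hangs on a global score.** A reader might infer that readiness for further testing rests on it. The documents give these scores a contextual role, attach no threshold to them, and refer readiness to the integrated results. Evaluation of the assembled app is left to later work.
- **The 1 SD deficit is hypothetical.**

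The reply does not remove the mismatch between the stated scope of the measures and what participants saw. Nor do the per-video ratings fully substitute. As described, they cover relevance, appropriateness, clarity, usefulness, helpfulness and motivation, and the integration section gives low cultural relevance as an example of a video-level rating. Neither description lists credibility, and the dedicated credibility/expectancy and cultural-competence instruments are given only once, after one set.

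**Conclusion.** The point holds as a misdescription with a modest analytic consequence. The documents assign the three measures a whole-intervention scope that a one-fifth exposure cannot give. A score pooled over sets would be a valid average of five set-specific ratings, but it would show only about one fifth of a deficit confined to one set, or roughly one quarter to one eighth over the splits examined. The expected fifth needs only random assignment. The range also assumes that the quota ran within subgroup and uses assumed subgroup sizes. Severity is minor to moderate: the study is descriptive and formative, other data can flag weak content, and no threshold depends on these scores.

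**What to change.** 1. In Quantitative Data and in the mixed-methods section, describe the three measures as ratings given after viewing one 4-video topic set.
2. Report each measure descriptively by assigned set, with n, mean, SD and an interval, beside an equally weighted average over the five sets. Equal weighting keeps unequal set sizes from driving the summary.
3. Use the set-level results when identifying components low on credibility or cultural fit, and read them with the per-video ratings and interviews.
4. Add to Limitations that each participant saw one fifth of the content, so no rating comes from someone who saw the full programme.

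This needs no new data, provided the Qualtrics assignment was kept. The cost is one extra table, imprecise set-level estimates (about ±0.53 SD at n = 16) and a more modest claim.

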#### Qualitative Data

After completion of the semistructured interviews, transcriptions were reviewed by the research team and assessed for saturation of concepts. Thematic analysis will be conducted following Braun and Clarke [68]. Qualitative data captured participant perspectives on cultural relevance, clarity, engagement, linguistic appropriateness, perceived usefulness, and suggested modifications for each video and for the intervention overall. Qualitative interview questions followed completion of the Perception of Intervention Content measure for each video, allowing participants’ narratives to be interpreted in relation to their quantitative ratings. Attention will be given to qualitative explanations corresponding to the Perception of Intervention Content measure items with lower ratings in analyses, as these provide direct guidance for targeted content modification. The multidisciplinary qualitative team will develop the codebook and then code the transcribed interviews in 2 coding passes: first by interview question and then for higher-level concepts and theoretical constructs identified in the first coding pass. The 2 interview coders will code 2 interviews independently and then review them with the qualitative researcher ([name]). Any discrepancies will be discussed and revised as needed. If there is good correspondence, the remaining interviews will be divided between the 2 coders, coded independently, and then reviewed by the other coder. Finally, the qualitative researcher will review the coding, and the team will meet to discuss and reach consensus on any areas of disagreement. Coded transcripts will then be analyzed for themes and subthemes. Next, the thematic analysis process will be reviewed by another member of the team to assess the trustworthiness of the data analysis process and review the coded transcripts for confirming and disconfirming evidence of themes. The themes and subthemes will be triangulated with quantitative data and then analyzed by geographic subgroup, as applicable.

#### Mixed Methods Integration (Triangulation)

A triangulation mixed methods data analysis approach [69,70] will be used to integrate quantitative and qualitative findings to guide intervention refinement (see Figure 2). Points of integration will be identified through alignment of corresponding qualitative interview questions and quantitative measures, followed by identification of additional conceptual integration points. Integration will occur at the level of video content and thematic domains and will examine qualitative themes alongside quantitative ratings to identify convergence, complementarity, or divergence across data sources.

**Figure 2. F2:**
[figure not shown]
Mixed methods integration framework.

Lower Perception of Intervention Content ratings will be examined alongside participants’ explanations to identify specific content elements contributing to reduced clarity, relevance, or motivational impact. Global acceptability measures will contextualize overall perceptions of intervention credibility, usefulness, and cultural appropriateness across intervention materials. For example, videos receiving lower quantitative ratings (eg, clarity or cultural relevance) will be reviewed alongside corresponding qualitative feedback to determine specific revision targets.

Integrated findings will be synthesized into actionable revision targets, with priority given to content areas showing convergence between lower quantitative ratings and recurrent qualitative suggestions. Content demonstrating consistently favorable ratings and minimal suggested changes will be retained. Integrated results will directly inform iterative refinement of intervention materials and determination of readiness for subsequent feasibility and implementation testing.

